The first-trimester prediction model developed by the Fetal Medicine Foundation (FMF), integrating maternal factors, mean arterial pressure (MAP), uterine artery pulsatility index (UtAPI), and PlGF, identifies approximately 90% of early preeclampsia (requiring delivery <32 weeks), 75% of preterm preeclampsia (delivery <37 weeks), and 41% of term preeclampsia cases at a 10% screen-positive rate [22]. This approach also detects 56% of early small for gestational age (SGA; delivery <32 weeks) and 46% of preterm SGA (delivery <37 weeks) neonates [23]. Clinical trials have demonstrated that prophylactic aspirin (>100 mg) combined with the first-trimester prediction model effectively prevents preterm preeclampsia and its associated adverse outcomes [24].

Despite these advances, predicting and preventing late-onset or term preeclampsia and FGR remains challenging due to their heterogeneous pathophysiology. These conditions exhibit less pronounced angiogenic biomarker alterations and weaker associations with placental dysfunction than early-onset cases [25]. Although causing fewer adverse outcomes, term complications have a higher prevalence, thus constituting a substantial health care burden [26]. Furthermore, low-dose aspirin appears to be less effective in preventing term preeclampsia [24]. Recent research proposes that risk stratification at 35 to 36 weeks of gestation with planned birth may offer a potential preventive strategy for managing term preeclampsia [27]. However, determining optimal delivery timing based on individualized risk stratification requires more investigation. Emerging evidence links maternal cardiovascular maladaptation and altered hemodynamic profiles with preeclampsia and FGR development, providing new directions for improving prediction models [28,29]. Current research remains limited on combining hemodynamic measurements with placental dysfunction markers to enhance prediction accuracy.

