This prospective cohort study aims to develop enhanced prediction models for placental dysfunction–related complications and define optimal delivery timing. Candidate predictors will be selected a priori based on four guiding principles: (1) established inclusion in validated prediction models and current screening approaches (maternal characteristics, MAP, uterine artery Doppler, and angiogenic biomarkers used in the FMF prediction models), (2) biological plausibility and prior evidence linking placental dysfunction and maternal cardiovascular maladaptation with preeclampsia and FGR (eg, ophthalmic artery Doppler and arterial stiffness measures), (3) feasibility of implementation within routine maternity care pathways, and (4) the potential incremental predictive value of novel biomarkers derived from stored biospecimens and exploratory omics approaches. By integrating clinical factors, biophysical parameters, and maternal circulating biomarkers across 3 critical gestational windows, this study will improve risk stratification and guide clinical decision-making in perinatal care. Furthermore, the comprehensive dataset and biobank will facilitate investigation of novel biomarkers and pathophysiological mechanisms underlying placental dysfunction.

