### Study Objectives

#### Primary Objectives

The primary objectives of this study are as follows:

To improve current predictive models or develop new predictive models for placental dysfunction–related pregnancy complications, including preterm preeclampsia and FGR, at 2 critical gestational periods: the first trimester (11‐13 weeks) and the second trimester (26‐28 weeks)To establish third-trimester (35‐36 weeks) models to predict term preeclampsia and FGR and to define the optimal time for delivery.

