#### Primary Objectives: Prediction Model Development

Multivariable logistic regression will serve as the primary analytical approach for prediction model development at 3 gestational windows (11‐13 weeks, 26‐28 weeks, and 35‐36 weeks of gestation) to address both primary objectives 1 and 2. Clinically relevant candidate predictors are predefined and entered into multivariable models, followed by model reduction to achieve parsimony (eg, backward elimination with a retention threshold of *P*<.10). Nonlinear relationships between continuous variables and the log odds of the outcomes will be tested with the inclusion of polynomial terms up to the third degree, which will be kept in the model if statistically significant.

For each patient, this method estimates a predicted probability of developing the outcome based on the log odds of the outcome. For primary objective 1, the predicted probabilities can be used to define low- and high-risk subgroups at predefined gestational age thresholds. Specifically, a risk threshold will be defined based on clinically relevant screen-positive rates (eg, 10%, 15%, or 20%) to balance sensitivity and specificity for clinical implementation. For primary objective 2, logistic regression will similarly provide predicted probabilities. In addition, Fine and Gray competing risks time-to-event models will be used as sensitivity analyses accounting for delivery without the outcome of interest (preeclampsia or FGR) as a competing event.

To further improve upon current FMF prediction models, a Bayesian updating approach will be applied to refine existing FMF first-trimester risk estimates using additional biomarkers and clinical variables collected later in pregnancy. The FMF first-trimester risk estimate will be used as the prior probability. Likelihood ratios derived from biomarker and biophysical measurements at 26 to 28 weeks and 35 to 36 weeks will be incorporated via Markov chain Monte Carlo simulations to generate updated posterior risk distributions. This enables dynamic, individualized risk reassessment as pregnancy progresses.

All models will undergo internal validation using 5-fold cross-validation with repeated iterations to obtain stable performance estimates. Model performance will be evaluated using the following metrics:

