#### Secondary Objective Analysis

For secondary objective 1, time-to-event analyses will be used to evaluate the association between predicted risk scores and adverse maternal and perinatal outcomes after diagnosis of complications. For secondary objective 2, AUC-ROC analysis, sensitivity and specificity, and predictive values will be used to assess the individual predictive performance of each biomarker candidate. For secondary objective 3, longitudinal biomarker trajectories will be compared between participants with the outcomes of interest and those without these outcomes using linear mixed-effects models with random intercepts and slopes for each participant. Exploratory proteomics and metabolomics analyses will be performed on a subset of samples to identify novel biomarkers and biological pathways associated with placental dysfunction.

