This project aims to enhance existing prediction models for term preeclampsia and SGA through the evaluation of additional biomarkers across 3 critical gestational stages, investigating both routine antenatal measurements and specialized markers of placental and cardiovascular dysfunction, including Doppler ultrasound parameters, maternal hemodynamic indices, and angiogenic markers. Doppler ultrasound assessment of uterine arteries can reflect placental perfusion status, with elevated values indicating increased resistance and impaired placental blood flow [57,58]. Maternal hemodynamic parameters, including ophthalmic artery Doppler indices, MAP, and augmentation index, provide insights into cardiovascular adaptation and peripheral vascular function [59-61]. Angiogenic markers (sFlt-1, PlGF, and the sFlt-1:PlGF ratio) indicating angiogenic imbalances serve as biochemical predictors of placental dysfunction [20,62,63] and spontaneous preterm labor [64]. Furthermore, our study establishes a valuable biobank for identifying novel molecular biomarkers and investigating underlying mechanisms of placental dysfunction through omics techniques. Incorporating these diverse markers and novel biomarker candidates into existing prediction models has the potential to enhance accuracy for late-onset pregnancy complications.

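### The study aims to improve existing prediction models by adding biomarkers, but no stated analysis measures how much a marker adds

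*Protocol article*

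**What the plan says.** **The aim.** The first primary objective is "To improve current predictive models or develop new predictive models for placental dysfunction–related pregnancy complications". The Introduction names a gap: "Current research remains limited on combining hemodynamic measurements with placental dysfunction markers to enhance prediction accuracy". One of its four principles for choosing candidate predictors is "the potential incremental predictive value of novel biomarkers derived from stored biospecimens and exploratory omics approaches". The Discussion states that "Incorporating these diverse markers and novel biomarker candidates into existing prediction models has the potential to enhance accuracy", and presents the evaluation of additional biomarkers as the means of enhancing existing models for term preeclampsia and SGA. The model development section introduces Bayesian updating as a way to improve further on the FMF models.

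**The analyses.**
- Secondary Objective Analysis, objective 2: "AUC-ROC analysis, sensitivity and specificity, and predictive values will be used to assess the individual predictive performance of each biomarker candidate".
- Primary Objectives: Prediction Model Development: "Clinically relevant candidate predictors are predefined and entered into multivariable models, followed by model reduction to achieve parsimony", with backward elimination at P<.10 given as an example. The FMF first-trimester risk also serves as a prior, updated with marker likelihood ratios from the two later windows.
- Performance metrics: discrimination, calibration, sensitivity, specificity, predictive values and screen-positive rates. The comparison item names only NICE and ACOG.

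The Discussion calls the FMF model the most effective method for early-onset and preterm preeclampsia and superior to risk-factor checklists. It also says that the hospital already screens with it routinely.

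**The concern.** Where FMF-based screening is already in use, a new marker is worth measuring only for what it adds to that risk. A marker's own AUC mixes what it adds with what it shares with maternal factors, MAP, UtAPI and PlGF. A high value may therefore reflect mostly shared information, and a modest value may hide a useful independent contribution.

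The study could report all its planned results and still give no estimate of the gain over current screening. Beating NICE or ACOG would not supply one, because the article itself reports that FMF already outperforms checklists. The anticipated publications include an evaluation of maternal circulating biomarkers. Readers of stand-alone AUCs there could easily take them as evidence of added value.

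**Working it through.** **Step 1. Does any stated analysis yield an increment?**

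| Stated analysis | What it yields | With-versus-without-marker estimate? |
|---|---|---|
| Objective 2, each biomarker alone | Stand-alone AUC, sensitivity, specificity, predictive values | No |
| Multivariable logistic model with reduction | Retained or dropped, conditional on the other predictors | No. A P value gives no size of improvement. Reduction may also remove base predictors, so the final model need not contain the base model |
| Bayesian updating of FMF risk | Updated posterior risks | No. No comparison with the un-updated FMF risk in the same women is stated |
| Named comparators | Performance against NICE and ACOG | No. FMF is not listed |

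**Step 2. How far can stand-alone AUC and added value diverge?** The article gives no figure on this point to reproduce. Its sample size of about 1700 does not enter. All inputs below are assumptions, except the second base AUC of 0.75, which is the target AUC in the Sample Size Estimation section.

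The model is binormal with equal variances. Write z(A) for the standard normal quantile of an AUC A; the separation is d = √2 × z(A).

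- Fully redundant marker, within-class correlation ρ with the base score: AUC = Φ(ρ × z_base). Its true increment is zero.
- Marker with correlation r: z_comb² = (z_base² + z_m² − 2 r z_base z_m) / (1 − r²), and combined AUC = Φ(z_comb).
- Detection at a 10% false-positive rate: Φ(d − 1.282).

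*Base AUC 0.80:* z_base = 0.842, d = 1.190, detection Φ(−0.091) = 46.4%.

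- Redundant marker: ρ = 0.5 gives Φ(0.421) = 0.663; ρ = 0.6 gives Φ(0.505) = 0.693; ρ = 0.8 gives Φ(0.673) = 0.750. The gain is 0.000 in each case.
- Marker with AUC 0.60 (z_m = 0.253), r = 0: z_comb = √(0.708 + 0.064) = 0.879, AUC 0.810, d = 1.243, detection Φ(−0.039) = 48.5% (0.4846, so 48% to the nearest point).
- Same marker, r = 0.2: z_comb = √((0.7725 − 0.0853)/0.96) = 0.846, AUC 0.801, detection 46.6%.

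*Base AUC 0.75:* a redundant marker with stand-alone AUC 0.70 (ρ = 0.78) adds 0.000. A marker with AUC 0.62 raises the base to 0.771 at r = 0 (gain 0.021) or 0.757 at r = 0.2 (gain 0.007).

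*Base AUC 0.90:* a redundant marker with ρ from 0.5 to 0.8 shows a stand-alone AUC of 0.74 to 0.85.

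In the first two settings, the marker with the higher stand-alone AUC adds nothing and the one with the lower AUC adds a little.

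**The case against.** There are four serious points on the other side.

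1. *The analysis matches its objective.* Secondary objective 2 asks for the predictive value of clinically tested biomarkers, not their incremental value. The explicit wording, "the potential incremental predictive value of novel biomarkers derived from stored biospecimens", is a principle for choosing predictors and concerns novel markers. This stands: the objective 2 analysis is not wrong for its own wording. The gap lies between the study's wider aim and the full set of stated analyses.

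2. *No stated rule ranks markers by stand-alone AUC.* A reader might infer that useless markers would be carried forward because their own AUC is high. The documents do not support that. Candidates are chosen a priori and reduced conditionally on the other predictors, a step that would tend to drop a redundant marker. The risk is one of interpretation, not of a faulty selection rule.

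3. *Markers are combined with existing predictors.* They are, in the multivariable models and the FMF updating, and all models are to be cross-validated. The Abstract also promises comparison with existing approaches. But the Methods name only NICE and ACOG, and the performance of a combined model is not an increment until it is set against the base in the same women.

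4. *This is a condensed article, and a fuller analysis plan may give the metric.* That is possible, and the choice of test statistic or interval would normally be left to such a plan. The point here rests on what the article does fix: the marker-level measures and the list of comparators.

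**Conclusion.** The concern holds in a limited form. Improvement on existing models is an aim of the study, yet no analysis stated in the article measures it for any marker, and the model that the article itself rates best is absent from the named comparators. The stand-alone analysis should stay, but it cannot bear a conclusion about added value.

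The size is illustrative. With an assumed base AUC of 0.80, zero added value is compatible with a stand-alone AUC of 0.66 to 0.75. A marker with AUC 0.60 can add up to about 0.01 in AUC and two percentage points of detection if it is independent of the base, and almost nothing at a correlation of 0.2. These results rest on equal-variance binormal scores and on pairing a fully redundant marker with a largely independent one. Real markers will lie between. The direction of the argument does not depend on the exact values.

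The change should be made before the biomarker results are reported, but it does not call any planned analysis invalid.

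**What to change.** Keep the stand-alone AUCs as descriptive results and add a nested comparison, for each window and outcome, in the same women:

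- **Base:** the FMF risk, or a base model with maternal factors, MAP, UtAPI and PlGF. When PlGF is the marker under study, use the base without it.
- **Extended:** the same base plus the marker, with the base terms kept in and not subject to elimination.
- **Report:** the likelihood-ratio test, and the cross-validated change in AUC and in detection rate at a fixed screen-positive rate (the article already names 10%, 15% and 20% as examples), with intervals.
- **Comparators:** add the FMF risk to NICE and ACOG in the performance list, and compare the Bayesian-updated risk with the un-updated FMF risk.

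This needs a few sentences in the plan and modest extra analysis of variables that Table 1 already lists. Women may join at any stage before 37 weeks, so each comparison should state how many women have both the base predictors and the marker. The price is that increments will probably be small, with wide intervals, and less striking than stand-alone AUCs.

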### Dissemination

The results of this study will be disseminated through publications in peer-reviewed scientific journals and conference presentations. We will codevelop a dissemination plan with Gold Coast Health and Hospital Service and consumers to communicate the project’s findings to key stakeholders (eg, consumers and policymakers). Additionally, participants have the option to receive a written summary of the study’s findings and future directions.

## Results

Recruitment for the Placental Health Study commenced in June 2022. By the close of recruitment in February 2026, a total of 1267 participants were enrolled. Of these, 1072 (84.6%) participants had a completed pregnancy, 144 (11.4%) participants are still to complete their pregnancy, and 51 (4%) had withdrawn or with missing or duplicated data. Comprehensive clinical data, including maternal demographics, medical and obstetric history, ultrasound measurements, Doppler indices, hemodynamic parameters, pathology laboratory results, and pregnancy outcomes, were collected through integration with electronic medical records (Table 1). Data were recorded in REDCap. Maternal serum, plasma, whole blood for RNA extraction, and urine samples have been collected and processed according to standardized operating procedures. Biospecimens are stored at −80 °C.

**Table 1. T1:** Summary of data and sample collection throughout pregnancy.

Assessment period and category	Data collected
At enrollment	
Demographic data	Date of birth, age, height, weight, BMI, ethnicity, smoking, and alcohol use status
Medical history	Diabetes mellitus, chronic hypertension, systemic lupus erythematosus, and antiphospholipid syndrome
Obstetric history	Miscarriage, termination, parity, previous preterm birth, preeclampsia, FGR^a^, placental abruption, and placenta previa
Risk assessment	Preeclampsia risk scoring (NICE^b^ and ACOG^c^ guidelines)
11‐13 weeks assessment	
First-trimester risk assessment	NIPT^d^ results (risk of trisomies, fetal sex, risk of monosomy X, sex chromosome aneuploidy risk, 22q11.2 deletion risk, and fetal fraction [cfDNA^e^, %], FGR risk, and preterm preeclampsia risk
Ultrasound and Doppler	Fetal biometry (CRL^f^ and NT^g^), fetal Doppler (ductus venosus A-wave), maternal Doppler (right and left uterine artery PI^h^ and mean PI), biophysical markers (cervical length and measurement method), and ultrasound markers (nasal bone, tricuspid regurgitation, cardiac activity, FHR^i^, holoprosencephaly, diaphragmatic hernia, atrioventricular septal defect, exomphalos, and megacystis)
BP^j^	Systolic BP, diastolic BP, and MAP^k^
Biochemical markers	Free beta-hCG^l^, PAPP-A^m^, PlGF^n^, sFlt-1^o^, and sFlt-1:PlGF ratio
Clinical pathology	Urine test, full blood count, chemistry panel, and recent iron infusion date (if available)
26‐28 and 35‐36 weeks	
Ultrasound and Doppler	Fetal biometry (BPD^p^, HC^q^, AC^r^, FL^s^, EFW^t^, and DVP^u^); biophysical markers (cervical length and measurement method and placenta position); fetal Doppler (umbilical diastolic flow, UA^v^ PI Dopplers, MCA^w^ PI Dopplers, ductus venosus A-wave, and ductus venosus Dopplers-PIV^x^); and maternal Doppler (right and left uterine artery pulsatility index and mean PI)
Maternal hemodynamics	Systolic BP, diastolic BP, MAP, augmentation index, and maternal ophthalmic artery Doppler (right and left PI, RI^y^, EDV^z^, PSV^aa^-1, PSV-2, and PSV-2:PSV‐1)
Biochemical markers	PlGF, sFlt-1, and sFlt-1:PlGF ratio
Clinical pathology	Urine test, full blood count, chemistry panel, and recent iron infusion date (if available)
GDM screening	Random glucose, HbA_1c_^ab^, OGTT^ac^ (fasting, 1-hour, and 2-hour values); and insulin or metformin use
At delivery	
Delivery details	Gestational age at delivery; onset of labor; type of rupture of membrane; PPROM^ad^; FBS^ae^ test results; delivery type; number of vessels in cord; antenatal, intrapartum, and postnatal blood loss; postpartum hemorrhage
Neonatal outcomes	Live birth or stillbirth, onset of respirations, birth weight, birth length, head circumference, sex, Apgar scores (1 and 5 minutes), resuscitation, cord gas analysis, and SCN^af^ or NICU^ag^ admission
Maternal outcomes	BP, postpartum hemorrhage, and adverse events
All visits	
Pregnancy complication and medication	Preeclampsia, GH^ah^, antepartum hemorrhage, threatened preterm labor, FGR, PPROM, GDM^ai^; gestational age at diagnosis; medication details (start and stop date and dose)
Biological sample collection	Plasma, serum, whole blood (in PAXgene RNA blood tube), and urine

a FGR: fetal growth restriction.

b NICE: National Institute for Health and Care Excellence.

c ACOG: American College of Obstetricians and Gynecologists.

d NIPT: noninvasive prenatal testing.

e cfDNA: cell-free DNA.

f CRL: crown-rump length.

g NT: nuchal translucency.

h PI: pulsatility index.

i FHR: fetal heart rate.

j BP: blood pressure.

k MAP: mean arterial pressure.

l hCG: human chorionic gonadotropin.

m PAPP-A: pregnancy-associated plasma protein A.

n PlGF: placental growth factor.

o sFlt-1: soluble fms-like tyrosine kinase-1.

p BPD: biparietal diameter.

q HC: head circumference.

r AC: abdominal circumference.

s FL: femur length.

t EFW: estimated fetal weight.

u DVP: deepest vertical pocket.

v UA: umbilical artery.

w MCA: middle cerebral artery.

x PIV: pulsatility index for veins.

y RI: resistive index.

z EDV: end-diastolic velocity.

aa PSV: peak systolic velocity.

ab HbA_1c_: hemoglobin A_1c_.

ac OGTT: oral glucose tolerance test.

ad PPROM: preterm premature rupture of membranes.

ae FBS: fetal blood sampling.

af SCN: special care nursery.

ag NICU: neonatal intensive care unit.

ah GH: gestational hypertension.

ai GDM: gestational diabetes mellitus.

A subset of samples has undergone preliminary biomarker quantification, including measurement of angiogenic markers (sFlt-1 and PlGF), and additional omics-based analyses are underway. Interim analyses have been conducted comparing clinical variables and biomarkers between participants with and without complications. It is anticipated that 2 to 3 primary publications will be ready in late 2026 or early 2027, including evaluation of maternal circulating biomarkers and exploratory analyses of novel biomarker candidates identified through omics techniques.

## Discussion

This protocol describes a prospective cohort study aimed at developing advanced prediction models for placental dysfunction–related pregnancy complications, allowing for dynamic and personalized accurate risk assessment throughout the pregnancy. First- and second-trimester prediction models aim to enhance early risk assessment for placental dysfunction–related complications (preeclampsia, FGR, preterm birth, and stillbirth), and the third-trimester model focuses on predicting the onset of term complications (preeclampsia and FGR) and determining optimal delivery timing. This comprehensive strategy advances personalized obstetric care through evidence-based risk stratification.

The FMF first-trimester prediction model shows superior performance compared with traditional risk-factor–based checklists [17]. By combining maternal factors with measurements of MAP, UtAPI, and serum PlGF, this model is the most effective method for predicting early-onset and preterm preeclampsia, achieving detection rates of 90% and 75%, respectively [22,43]. This model has been validated across diverse populations, consistently demonstrating predictive performance comparable to the original studies and has been tested in randomized clinical trials [24,44-48]. Importantly, when coupled with prophylactic low-dose aspirin administration starting before 16 weeks’ gestation in high-risk pregnancies, this screening strategy reduces preterm preeclampsia by more than 60% [24,49]. In addition, the model achieves detection rates of 56% for early SGA fetuses (<32 weeks) and 46% for preterm SGA neonates (<10th percentile), with aspirin use potentially reducing the incidence of preterm SGA by 20% and early SGA by 40% [23].

These advancements in preterm preeclampsia screening have prompted updates to national [50,51] and international [52] guidelines, recommending implementation of the prediction model with prophylactic low-dose aspirin to reduce preterm preeclampsia incidence and associated adverse outcomes. A cost-effectiveness analysis in Australia demonstrated significant benefits of this screening strategy, including prevention of 31 preterm preeclampsia cases and cost savings of approximately Aus $1.43 million (Aus $1=US $0.72 as of August 27, 2020) over a 2-year period [53]. Despite these clinical benefits, the FMF first-trimester prediction model has not yet become a standard component of routine maternity care for all health care providers in Australia. Gold Coast University Hospital has implemented FMF-based first-trimester preeclampsia screening in routine clinical care, providing a valuable setting to generate evidence supporting broader application in clinical practice.

Current prediction models still have limited accuracy for predicting term preeclampsia and SGA due to their complex etiology. Although considered less severe, term complications constitute most cases, occurring at least twice as frequently as preterm preeclampsia, and impose a significant health care burden [26]. While the first-trimester screening combined with low-dose aspirin effectively prevents preterm preeclampsia, it showed limited efficacy for term preeclampsia [24]. A prediction model at 35 to 36  weeks’ gestation, using maternal factors and biomarkers, can identify approximately 70% of pregnancies at risk of developing term preeclampsia [54]. In addition, planned birth at term is a potential prevention strategy for term preeclampsia [55,56]. A recent secondary analysis from a prospective nonintervention cohort study has demonstrated that a risk-stratified approach based on a combined prediction model at 35 to 36  weeks’ gestation with timed birth is likely able to reduce the risk of term preeclampsia [27]. However, research on individualized risk assessment models at late gestation to determine optimal delivery timing remains limited. This cohort study will facilitate the development of refined prediction models and optimal delivery timing strategies to reduce term preeclampsia incidence and improve pregnancy outcomes.

This project aims to enhance existing prediction models for term preeclampsia and SGA through the evaluation of additional biomarkers across 3 critical gestational stages, investigating both routine antenatal measurements and specialized markers of placental and cardiovascular dysfunction, including Doppler ultrasound parameters, maternal hemodynamic indices, and angiogenic markers. Doppler ultrasound assessment of uterine arteries can reflect placental perfusion status, with elevated values indicating increased resistance and impaired placental blood flow [57,58]. Maternal hemodynamic parameters, including ophthalmic artery Doppler indices, MAP, and augmentation index, provide insights into cardiovascular adaptation and peripheral vascular function [59-61]. Angiogenic markers (sFlt-1, PlGF, and the sFlt-1:PlGF ratio) indicating angiogenic imbalances serve as biochemical predictors of placental dysfunction [20,62,63] and spontaneous preterm labor [64]. Furthermore, our study establishes a valuable biobank for identifying novel molecular biomarkers and investigating underlying mechanisms of placental dysfunction through omics techniques. Incorporating these diverse markers and novel biomarker candidates into existing prediction models has the potential to enhance accuracy for late-onset pregnancy complications.

The key strength of this prospective cohort study lies in its comprehensive approach to implementing and improving the prediction of placental dysfunction–related complications throughout pregnancy, from first-trimester screening to late-gestation risk stratification in a general-risk population. The proposed dynamic prediction framework, if validated, could benefit implementation of targeted surveillance protocols and timely interventions, addressing current gaps in evidence-based obstetric care. Furthermore, the study establishes a valuable database and perinatal biorepository, providing valuable resources for novel biomarker discovery and investigation of associations between clinical phenotypes and biological mechanisms underlying maternal systemic changes and placental dysfunction. Some limitations should be considered. First, this study is limited to singleton pregnancies, which may restrict its applicability to multiple pregnancies. Second, the single-center design potentially constrains the generalizability of the findings to other populations and clinical settings. Third, despite incorporating diverse clinical, biochemical, and biophysical markers, some important predictors may remain unmeasured. In addition, some biomarkers in the final prediction models may be expensive or technically challenging to measure in routine clinical practice, potentially limiting widespread adoption. External validation in independent populations is planned as a future phase of research and will evaluate model transportability and generalizability across different clinical settings and populations. Despite the limitations, this research holds significant potential to advance our understanding of placental dysfunction–related pregnancy complications and enhance obstetric care through improved risk prediction and personalized intervention strategies.
